### Participant timeline

Participants in the trial are required to be recorded four times, with visits at enrollment (in the hospital), 4 weeks (in the hospital), 8 weeks (by telephone follow-up), and 12 weeks (in the hospital) after intervention, each taking approximately 15–20 min. In addition, participants are asked to have an additional telephone follow-up visit 1 month after completion of the study, regardless of the type of intervention (Table 4).

**Table 4 Tab4:** Time schedule of enrolment, intervention and outcome measures of the trial

Timepoint	Study period					
	Screeningstage	T0: 0–1 day Treatment (Baseline)	T1: 4 week treatment	T2: 8 week treatment	T3: 12 week treatment	T4: 1 month after end of treatment
Face-to-face meeting		**√**	**√**		**√**	
Enrolment						
Eligibility screening	**√**					
Informed consent	**√**					
Allocation	**√**					
Intervention						
Wangbi granules/Placebo		**√**	**√**	**√**	**√**	
Outcomes and measures						
Basic information		**√**				
DAS28		**√**	**√**	**√**	**√**	**√**
ACR50			**√**		**√**	
VAS		**√**	**√**	**√**	**√**	**√**
FS-14		**√**	**√**	**√**	**√**	**√**
HAQ-DI		**√**	**√**	**√**	**√**	**√**
Symptom score		**√**	**√**	**√**	**√**	**√**
Blood routine		**√**	**√**		**√**	
Urine routine		**√**	**√**		**√**	
Stool routine		**√**	**√**		**√**	
Electrocardiograph		**√**	**√**		**√**	
ALT/AST/Scr		**√**	**√**		**√**	
ESR/CRP		**√**	**√**		**√**	
RF/ACPA		**√**				
Blood samples		**√**			**√**	
Assessment of side effects			**√**	**√**	**√**	

*DAS28* disease activity score derivative for 28 joints, *ACR50* American College of Rheumatology 50% response criteria, *VAS* visual analogue scale for pain, *FS-14* fatigue scale-14, *HAQ-DI* health assessment questionnaire disability index, *ALT* alanine aminotransferase, *AST* aspartate aminotransferase, *Scr* serum creatinine, *ESR* erythrocyte sedimentation rate, *CRP* C-reactive protein, *RF* rheumatoid factors, *ACPA* anti-citrullinated protein antibodies

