### Recruitment

A total of 340 patients will be recruited from the 6 centers participating in this study. An investigator, assisted by a trained study coordinator at each participating center, will identify potential eligible patients based on the eligibility criteria. They will work with the attending physician to determine whether the patient is eligible for the trial. Patients who travel to outpatient or inpatient settings for RA are evaluated for eligibility by an investigator who collects relevant information face-to-face with the patient’s verbal consent at the time of treatment. If RA patients are recruited from posters, the internet, etc., eligibility will be assessed over the phone. After the patient is deemed to meet the criteria for participation, the investigator will inform the study protocol in detail, at which point potential participants can ask their questions and requests, and after formally signing written informed consent, they are enrolled in the trial as participants.

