### Outcomes

The efficacy of Wangbi granule will be observed and the main outcome is DAS28 [19], assessed by a dedicated rheumatologist (associate senior physician or better). The changes in the DAS28 score will be recorded during the observation period. Moreover, participants are considered to have achieved deep clinical remission when the calculated DAS28 score is lower than 2.6.

Secondary outcomes include patient-reported outcomes (symptom score) [18], ACR50 [20], fatigue scale-14 (FS-14) [21], visual analogue scale for pain (VAS) [22], health assessment questionnaire disability index (HAQ-DI) [23] and biological markers [24] such as CRP and ESR. Specific secondary outcomes are shown in Table 3.

**Table 3 Tab3:** Secondary outcomes of the trial

Secondary outcomes	
ACR50	ACR response was used to evaluate improvement in RA. ACR response requires the collection of the degree of improvement in the number of joints with pressure pain and the degree of improvement in the number of joints with swelling and the degree of improvement in 3 of the following 5 items: patient’s assessment of pain, patient’s overall assessment of disease activity, physician’s overall assessment of disease activity, patient’s assessment of physical function (HAQ), and values of acute phase reactants (ESR, CRP). Percentage improvement in each indicator = (pre-treatment value − post-treatment value)/pre-treatment value * 100% ACR20: ≥ 20% improvement in joint pain and swelling, and ≥ 20% improvement in at least 3 of the other 5 items ACR50: ≥ 50% improvement in joint pain and swelling, and ≥ 50% improvement in at least 3 of the other 5 items ACR70: ≥ 70% improvement in joint pain and swelling, and ≥ 70% improvement in at least 3 of the other 5 items
VAS	Patients’ joint pain levels were evaluated using the VAS, expressed on a ten-point scale, with higher scores indicating more intense pain Face-to-face or telephone follow-ups were conducted at baseline, 4 weeks, 8 weeks, and 12 weeks of treatment, and patients were scored based on their subjective perceptions

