FS-14	FS-14 is used to measure the patient’s fatigue level. FS-14 was divided into 2 dimensions: physical fatigue (8 items) and mental fatigue (6 items). The scoring method is based on a 2-point scale, with 0 points for “No” and 1 point for “Yes”, and reverse scoring for items 10, 13 and 14, with a total score of 0 to 14 points, with higher scores representing heavier fatigue Face-to-face or telephone follow-ups were conducted at baseline, 4 weeks, 8 weeks, and 12 weeks of treatment, and patients were scored based on their subjective perceptions
HAQ-DI	The HAQ-DI was used to assess the overall functional status of the patients. The questionnaire consists of 20 questions containing 8 areas of daily activity, with higher scores on each question representing poorer functioning Face-to-face or telephone follow-ups were conducted at baseline, 4 weeks, 8 weeks, and 12 weeks of treatment, and patients were scored based on their subjective perceptions
Symptom score	The patient’s symptoms associated with RA were recorded, including joint swelling, pressure pain, activity level, diet, etc. The greater the degree of performance of each symptom, the higher the score Face-to-face or telephone follow-ups were conducted at baseline, 4 weeks, 8 weeks, and 12 weeks of treatment, and patients were scored based on their subjective perceptions
Biological markers	All patients will have their venous blood and other required specimens collected on an empty stomach in the early morning of the specified date and tested in the testing department of each research center, and the biological samples will be frozen in a special refrigerator in China-Japan Friendship Hospital Routine blood, urine, and stool tests were performed at baseline, 4 weeks, and 12 weeks of the trial Electrocardiograph, ALT, AST, and serum creatinine were tested at baseline, 4 weeks, and 12 weeks of the trial to monitor the safety of drug administration ESR and CRP were measured at baseline and 12 weeks of the trial to monitor inflammation levels RF and ACPA were tested during the baseline period of the trial to determine the patient’s antibody levels Additional blood samples were collected at baseline, week 12 of the trial and used to test for various proteins and genes such as inflammatory cytokines

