### Statistical analysis

All analysis and data visualization will be performed using IBM SPSS (Version 25.0), R (Version 4.1.1).

Baseline data will be displayed using descriptive statistics (eg, means, SD, median, IQR, proportions). We will test the group balance achieved by randomization through appropriate statistical tests (eg, Student’s t tests, Pearson’s χ^2^ tests). Outcomes with a continuous distribution will be compared between groups using the mean (Student’s t test) and Pearson’s χ^2^ test will be used for binary categorical data where categorical variables are expressed as frequencies and percentages and continuous variables are expressed as means and SD.

Preliminary statistical analysis of the primary outcome data will be performed according to the intention-to-treat principle, and the changes in DAS28 will be compared between patients treated with Wangbi granule and Wangbi placebo, and report the rate of deep remission. Further, two-way repeated measures analysis of variance (ANOVA) will be used to examine any interaction effects of the outcome variables between the two groups at the four time points. Mauchly’s sphericity test will be used to examine the spherical assumptions of the repeated measures ANOVA. Bonferroni-corrected post hoc multiple comparisons will be used to examine simple effects between groups at different time points and at different time points for each group.

Sensitivity analysis will be an essential part of the statistical analysis process to complement the interpretation of the results. Depending on the specifics of the data, the full samples will be divided into subgroups based on information about additional drugs (e.g. NSAIDs), co-existing underlying conditions (e.g. hypertension, diabetes), long-term use of other drugs, etc. The calculations will be re-run in each subgroup to verify the validity of the results. When necessary, a per protocol set (PPS) analysis will be part of the sensitivity analysis. If any variable has no more than 20% missing values, the MICE package in R will be used for multiple interpolation to replace it. For the statistical process, *P* < 0.05 is considered statistically significant.

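### DAS28 is scheduled at two telephone contacts without ESR/CRP, so the four-time-point repeated-measures ANOVA of DAS28 needs a week-8 value that cannot be obtained as defined

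*Protocol article*

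**What the plan says.** **Outcome.** The Outcomes section states that "the main outcome is DAS28 [19], assessed by a dedicated rheumatologist (associate senior physician or better". Quality control adds that two investigators rate the participant at each follow-up visit and their scores are averaged.

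**Contact mode.** The Participant timeline has hospital visits at enrollment and week 4, then "8 weeks (by telephone follow-up), and 12 weeks (in the hospital) after intervention". After that, "participants are asked to have an additional telephone follow-up visit 1 month after completion of the study". In Table 4 the row "Face-to-face meeting" is ticked at T0, T1 and T3 only.

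**Schedule.** Table 4 ticks DAS28 at T0, T1, T2, T3 and T4. It ticks ESR/CRP at T0, T1 and T3. Table 3 differs on the laboratory schedule: "ESR and CRP were measured at baseline and 12 weeks of the trial to monitor inflammation levels".

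**Analysis.** Statistical analysis first compares the change in DAS28 between groups by intention to treat and reports the deep remission rate. It then adds a two-way repeated-measures ANOVA to examine "any interaction effects of the outcome variables between the two groups at the four time points", with Bonferroni-corrected comparisons at each time point. Multiple imputation is allowed for a variable with up to 20% missing.

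**The concern.** DAS28 is a clinic score: a 28-joint assessment by a physician, combined with an acute-phase reactant. Table 4 asks for it at two contacts where there is neither an examination nor a blood test.

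The site must then do one of two things at week 8, and they have different consequences:

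- **Leave the value blank.** The time point is missing by design for everyone, and a standard repeated-measures ANOVA, which keeps only participants with all time points, has nobody left for DAS28.
- **Enter a substitute**, for example patient-reported joints with an older ESR or CRP. The model then runs, but one of its four levels is a different measure. A time effect or a group-by-time interaction around week 8 could reflect the change of method. Entry is limited to DAS28 2.6 to 3.2, a window of 0.6 points, and the target difference is 0.5, so even a modest shift between methods would be large on this scale.

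The conflict between Tables 3 and 4 puts the week-4 value in doubt as well.

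**Working it through.** No sample-size or power figure is involved. The check sets the schedule entries side by side.

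| Contact | Mode (text) | Face-to-face tick | ESR/CRP, Table 4 | ESR/CRP, Table 3 | DAS28 tick | ACR50 tick |
|---|---|---|---|---|---|---|
| T0 baseline | hospital | yes | yes | yes | yes | no |
| T1 week 4 | hospital | yes | yes | no | yes | yes |
| T2 week 8 | telephone | no | no | no | yes | no |
| T3 week 12 | hospital | yes | yes | yes | yes | yes |
| T4 1 month after | telephone | no | no | no | yes | no |

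**Step 1: obtainable values.** DAS28 is scheduled 5 times. Contacts with DAS28, a face-to-face meeting and ESR/CRP number 3 under Table 4 (T0, T1, T3) and 2 under Table 3 (T0, T3). So 5 − 3 = 2 scheduled values (T2, T4) cannot be obtained as defined, or 5 − 2 = 3 if Table 3 governs.

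**Step 2: which four time points.** The Participant timeline describes four recordings, at enrollment and weeks 4, 8 and 12, which are T0 to T3. Week 8 is therefore in the ANOVA and T4 is not. Another choice would not help: only 3 of the 5 contacts are in person, so any four include at least 4 − 3 = 1 telephone contact.

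**Step 3: amount missing if week 8 is left blank.** With 340 participants and four time points there are 340 × 4 = 1,360 DAS28 cells.

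- Week-8 DAS28 taken as a variable: 340/340 = 100% missing.
- DAS28 pooled over the four time points: 340/1,360 = 25% missing.
- If Table 3 governs and week 4 is lost too: 680/1,360 = 50% missing.

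Each figure exceeds the 20% limit, so the plan's own rule does not permit imputation. The number of participants with all four DAS28 values is 0.

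**Step 4: comparison with the protocol's other composite.** Table 3 builds ACR50 from joint counts and further items that include ESR/CRP. Table 4 ticks ACR50 only at T1 and T3, both in hospital with ESR/CRP. The schedule thus respects the measurement constraint for ACR50 and not for DAS28.

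**Step 5: the other scales.** Table 3 allows VAS, FS-14, HAQ-DI and the symptom score to be collected face to face or by telephone at baseline and weeks 4, 8 and 12. Their week-8 values are obtainable.

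**The case against.** The strongest defence is that the main result does not depend on week 8. The between-group comparison of DAS28 change comes first in the plan and the repeated-measures ANOVA is supplementary to it. Week 12 is an in-hospital visit with ESR/CRP under both tables. That stands, and it limits the seriousness of the point.

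It might also be said that an article condenses the full protocol, which could define a telephone DAS28. The silence of Table 3 proves little, since that table lists only secondary outcomes. But the difficulty is not an omission: the printed schedule contradicts the printed contact mode and the printed assessor.

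Several stronger readings are tempting and are not supported:

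- **That the whole repeated-measures analysis fails.** Only its DAS28 part does (Step 5).
- **That the 1-month value damages the ANOVA.** T4 is a schedule error, but it lies outside the four time points.
- **That week 4 is certainly lost.** Table 4 is consistent with itself there, with a hospital visit, ESR/CRP and ACR50 all ticked. The documents show a conflict between tables and do not say which is right.
- **That the primary comparison is compromised.** Data management uses the last recording as final data for participants who withdraw, so a telephone DAS28 could be carried forward for someone leaving between weeks 8 and 12. The documents give no timing for the assumed 10% loss, so this cannot be sized. It does not touch scores measured at week 12, and it disappears once the week-8 tick is removed.
- **That patients are randomised before DAS28 and laboratory values are known.** For poster and internet recruits the Recruitment section says "eligibility will be assessed over the phone", and Table 4 puts the Allocation tick under screening, while DAS28, ALT/AST and Scr are first ticked at T0. However, Allocation and blinding has each centre determine eligibility and obtain written consent before it requests a randomisation number. The T0 ticks record baseline outcomes and do not show that nothing was measured at screening. What remains is wording to reconcile.

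**Conclusion.** The point holds, limited to DAS28 at the telephone contacts. Two of five scheduled values (T2, T4) cannot be obtained as the protocol defines them. One of the four levels of the DAS28 repeated-measures ANOVA (week 8) is affected in all 340 participants, and a second (week 4) is in doubt until Tables 3 and 4 agree. That analysis cannot be run as written without either a level missing for everyone or an undefined substitute.

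The conclusion rests on two assumptions. First, DAS28 needs an examined joint count and ESR or CRP. The article does not print the formula, but this is the score's standard definition and fits the assessor requirement. Second, the four time points are T0 to T3, although Step 2 shows that any other four would also include a telephone contact. That the main comparison is unaffected assumes that the final DAS28 score in the sample size section means week 12; no visit is named, and the last DAS28 tick in Table 4 is T4.

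This should be fixed, but it does not threaten the trial's main result.

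**What to change.** 1. In Table 4, remove the DAS28 ticks at T2 and T4. Keep VAS, FS-14, HAQ-DI and the symptom score there.
2. In Statistical analysis, restrict the longitudinal DAS28 analysis to the in-hospital visits with ESR/CRP (T0, T1, T3). Name week 12 as the time point for the primary comparison and the remission rate. Leave the four-point analyses of the patient-reported scales as they are.
3. Reconcile Tables 3 and 4 on week-4 ESR/CRP so that week-4 DAS28 can be computed.
4. As a minor consistency edit, bring the telephone eligibility wording in Recruitment and the position of the Allocation tick in Table 4 into line with Allocation and blinding.

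The cost is edits to two tables and a few sentences, and the loss of the nominal week-8 and off-treatment DAS28 values, which cannot be validly measured by telephone. If the sponsor wants those values, the alternative is to make T2 and T4 in-person visits with ESR/CRP, at the price of two more clinic attendances per participant.

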### Sample size calculation

The study used superiority design approach. Due to the lack of clinical studies of methotrexate and tofacitinib in combination with Wangbi granule, we refer to the previous studies of methotrexate in combination with Wangbi granule for the treatment of RA [25]. In order to observe the deep remission effect of the Wangbi granule on RA condition, the final DAS28 score of the intervention group needs to be at least 0.5 points lower than that of the control group, so the cut-off value δ takes − 0.5. We adopted single-sided calculation whereα is 0.025, β is 0.2, and the sample size is 1:1, then the single group sample size of 155 cases is obtained. Considering a shedding rate of 10%, 170 cases are needed in each group, and the final total sample size is 340.According to the plan, as the lead center, China-Japan Friendship Hospital will complete the intake of 90 samples, and the remaining 5 centers will equally distribute the remaining 250 samples.

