### Eligibility criteria

Patients aged 18–75 years who meet the 1987 or 2010 international diagnostic criteria for RA are eligible for the study [16, 17]. Patients need to meet the diagnostic criteria (2018 edition) for “kidney deficiency and dampness” and “stasis blocking channels” in Chinese medicine [18]. The disease activity score derivative for 28 joints (DAS28) [19] score should be 2.6 to 3.2. The use of methotrexate (7.5–15 mg, quaque week, dose changes with disease) in combination with tofacitinib (5 mg, bis in die) for more than 12 weeks prior to recruitment is required. Before recruitment, clear notification and signing of informed consent are required.

Exclusion criteria include: taking immunosuppressants other than methotrexate and tofacitinib in the 3 months prior to recruitment; combination of other severe multi-system damaging diseases; presence of cognitive impairment, psychosomatic disorders, peripheral neurological disorders; those who are pregnant, breastfeeding, or have a planned pregnancy; overweight, allergic to the study drug, or enrolled in another clinical trial; other conditions in which the investigator believes the patient should not participate in the trial. The complete list of inclusion and exclusion criteria is provided in Table 1.

**Table 1 Tab1:** Inclusion and exclusion criteria of the trial

Inclusion criteria	Exclusion criteria

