All the botanical or zoological drugs that make up the Wangbi granule are explained in Table 2. All trial drugs will be manufactured and supplied by Liaoning Good Nurse Pharmaceutical (Group) Co., Ltd. (Benxi City, Liaoning Province, China) and tested by its quality management department to meet the Pharmacopoeia of China (2020 edition) grade standards. Voucher samples of all drugs will be stored at China-Japan Friendship Hospital (Beijing, China). The drug preparation and packaging will be operated by the pharmacy of Good Nurse Pharmaceutical in a fully enclosed production line. All ingredients will be mixed in the original dosage, steeped in pure water for 0.5 h, heated to boiling, decocted for 2 h, filtered from the aqueous extract, then the residue will be added to pure water and decocted for 1 h. The two liquid extracts will be combined, settled, filtered and concentrated into a thick paste (relative density 1.32–1.35, 50 °C), with a certain amount of soluble starch and dextrin as auxiliary materials to assist in forming, and processed into 1000 g concentrated granules by spray drying. The final Wangbi granule is equivalent to 27.88 g of the original drugs per 12 g (ter in die, a total of about 83.63 g per day) and sealed with aluminum-plastic composite film (BOPP/AL/CPE) packaging material. The Wangbi granule needs to be dissolved in hot water for each use. The placebo consists of one tenth of the dosage of Wangbi granule, starch, caramel color and bitter agent. Its appearance and odor are the same as those of Wangbi granule. The study drugs are from the same batch, purchased from Good Nurse Pharmaceutical (Liaoning, China), coded and kept under lock and key by the drug administrator in a special cabinet at room temperature and dry place. On the day of enrollment, patients will be given these medications.

**Table 2 Tab2:** Components of Wangbi granule (intervention drug)

Chinese name	Chinese Pinyin	Scientific name	Family	Part used	Original dosage (g)	Daily dosage(g)
生地黄	Sheng Di Huang	*Rehmannia glutinosa* (Gaertn.) DC.	Orobanchaceae	Dried root	196	7.056
熟地黄	Shu Di Huang	*Rehmannia glutinosa* (Gaertn.) DC.	Orobanchaceae	Steamed root	196	7.056
续断	Xu Duan	*Dipsacus asper* Wall. ex DC.	Caprifoliaceae	Dried root	147	5.292
附子	Fu Zi	*Aconitum carmichaeli* Debeaux	Ranunculaceae	Dried lateral root tuber	147	5.292
独活	Du Huo	*Angelica biserrata* (R.H.Shan & C.Q.Yuan) C.Q.Yuan & R.H.Shan	Apiaceae	Dried root	98	3.528

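### The sample size treats −0.5 DAS28 points as a threshold to be reached, but the planned test is against zero; the 10% loss allowance is also slightly short

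*Protocol article*

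**What the plan says.** All places are in the protocol article.

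- **Sample size calculation, design and error rates.** "The study used superiority design approach". "We adopted single-sided calculation whereα is 0.025, β is 0.2", with 1:1 allocation.
- **Sample size calculation, effect.** To show a deep-remission effect, the final DAS28 score in the intervention group "needs to be at least 0.5 points lower than that of the control group". The section then sets a cut-off value δ of −0.5. It gives no SD and no expected difference separate from δ. The inputs are referred to earlier studies of Wangbi granule with methotrexate, because studies that also used tofacitinib were lacking.
- **Sample size calculation, result.** "then the single group sample size of 155 cases is obtained". "Considering a shedding rate of 10%, 170 cases are needed in each group", which makes 340 in total.
- **Eligibility criteria.** The baseline DAS28 "score should be 2.6 to 3.2".
- **Statistical analysis.** Continuous outcomes are compared by Student's t test. The primary comparison is the change in DAS28 between arms by intention to treat, and P<0.05 counts as significant. Nothing in this section refers to 0.5.

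**The concern.** The effect is worded as a margin: a cut-off that the difference has to reach. The analysis asks a different question, namely whether the difference is zero. A significant t test supports the statement that the granule lowers DAS28 more than control. It does not support the statement that it lowers DAS28 by at least 0.5 more, which is what the sample size section says is needed. As written, a reader of the results cannot tell which statement a positive trial supports.

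The role of −0.5 also decides what 155 per group means. As a planning difference against a zero null, it fixes the SD that must have been used. As a margin, a second figure is needed, the true difference expected beyond the margin, and the section gives none.

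The step from 155 to 170 is a separate and smaller matter.

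**Working it through.** **Inputs.** δ = 0.5 in absolute value, one-sided alpha 0.025 (z = 1.960), power 80% (z = 0.842), 1:1 allocation, 155 per group, 10% loss, 170 per group, baseline window 2.6 to 3.2. No SD is stated, so 155 cannot be reproduced forwards. Formulas use the normal approximation. One-sided 0.025 and two-sided 0.05 share the same critical value, so sidedness is not the problem.

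**1. Reading A: −0.5 is the planning difference and the null is zero.** From n = 2·SD²·(1.960 + 0.842)²/0.5², solved for the SD:

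SD = 0.5 × √(155/2) / 2.802 = 1.571

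Put back in, SD 1.57 gives exactly 155. The noncentral t gives an SD of 1.566.

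*Compared with the entry window.* A score confined to 2.6 to 3.2 has an SD of at most 0.6/2 = 0.30, or 0.6/√12 = 0.17 if uniform. This bounds the baseline SD only.

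*Other SDs.* The SDs below 1.57 are assumptions, since the article gives none. The last column is the smallest observed difference reaching two-sided P<0.05 with 155 per group, 1.960 × SD × √(2/155).

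| SD | n per group for 80% power at 0.5 | Power with 155 | Smallest significant difference |
|---|---|---|---|
| 0.6 | 23 | >99.9% | 0.13 |
| 0.8 | 41 | >99.9% | 0.18 |
| 1.0 | 63 | 99.3% | 0.22 |
| 1.2 | 91 | 95.6% | 0.27 |
| 1.57 | 155 | 80% | 0.35 |

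An estimate below 0.5 can therefore be significant at every SD shown. For the 95% confidence interval to lie wholly at or beyond 0.5, the observed difference would have to be 0.5 plus the last column: 0.63 at SD 0.6, 0.72 at SD 1.0, 0.85 at SD 1.57.

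**2. Reading B: −0.5 is a superiority margin.** The null is then a difference of 0.5. If the true difference is exactly 0.5, the chance of rejecting is alpha, 2.5%, whatever the sample size. With 155 per group, 80% power needs a true difference of

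0.5 + SD × √(2/155) × 2.802,

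which is 0.69, 0.76, 0.82 and 0.88 for an assumed SD of 0.6, 0.8, 1.0 and 1.2. No single SD follows from 155 under this reading.

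**3. Loss allowance.**

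- 170 × 0.9 = 153, two short of 155.
- 155/0.9 = 172.2, so 173 per group and 346 in total.
- 155 × 1.1 = 170.5, which suggests that 10% was added to 155 and the result rounded down.
- 1 − 155/170 = 8.8%, the loss that 170 does cover.
- Power with 153 at difference 0.5 and SD 1.571: 0.5/(1.571 × √(2/153)) − 1.960 = 0.824, which gives 79.5%.

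**The case against.** **Sizing on a target difference and testing against zero is ordinary superiority practice.** That is so, and in any well-powered trial some estimates below the planning difference are significant. The article also never says it will claim a reduction of at least 0.5 on P<0.05 alone. What remains is that the sample size section does not call 0.5 an expected difference. It calls it a cut-off that the result has to reach, and no later section carries that requirement or withdraws it.

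**The SD may be in the full protocol.** It may, and its absence from an article is not the point. It matters here because 155 cannot be interpreted until the role of −0.5 is known.

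**An SD of 1.57 is not shown to be wrong.** This stands. The entry window limits baseline DAS28. It does not limit the week-12 score or the change, and flares could widen both. That 1.57 looks large for these patients is an inference.

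**The loss slip is immaterial.** Largely so. The analysis is by intention to treat, with multiple imputation for variables with up to 20% missing values, and the data management section uses the last record for withdrawn patients. The analysis set is thus not simply 153 completers. With all 170 analysed at SD 1.571, power would be about 83.5%, although imputed values do not carry full information.

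Two stronger readings are tempting:

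- *That the trial is underpowered, or that 80% power cannot be obtained on any reading.* The figures contradict this. Reading A gives 80% at SD 1.57 and more at any smaller SD. Reading B gives 80% if the true difference is large enough.
- *That the 0.5 should be discounted because the control preparation contains active product* ("The placebo consists of one tenth of the dosage of Wangbi granule"). The section defines 0.5 against the control group, which receives that preparation. A further discount would need a dose-response relation that the article does not give.

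**Conclusion.** The point holds in two parts.

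The main one is a mismatch between two stated sections: a −0.5 threshold that the difference has to reach, and a test against zero with no rule tied to 0.5. It affects what a positive result may be said to show. Under the planning-difference reading, observed differences of 0.13 to 0.22 (assumed SD 0.6 to 1.0), or 0.35 (SD 1.57), would be declared significant. Under the margin reading, the planned test does not address the margin, and a true difference of exactly 0.5 would meet it 2.5% of the time. The documents do not settle which reading was meant.

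The second part is plain arithmetic and minor: 170 per group with 10% loss leaves 153, costing about half a percentage point of power on completers at the implied SD.

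The implied SD of 1.57 belongs to the planning-difference reading only. If the true SD is smaller, the trial is larger than it needs to be for 0.5, not too small.

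**What to change.** Reword the sample size paragraph and add one sentence to the statistical analysis section.

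1. State whether −0.5 is the planning difference or a superiority margin.
2. If it is the planning difference, state that the null hypothesis is zero difference. Claim a reduction of at least 0.5 only if the upper limit of the two-sided 95% confidence interval for intervention minus control is at or below −0.5.
3. If it is a margin, test against −0.5 and state the larger true difference assumed.
4. Give the SD used, its source, and whether it refers to the final score (as in the sample size section) or to change (as in the analysis).
5. Restate power for 153 evaluable per group, or state that 170 per group covers about 8.8% loss.

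This needs no extra patients. The cost is a stricter condition on any claim of at least 0.5 and a slightly less favourable power or loss figure. If the margin reading was meant, the plan must also defend a true difference above 0.5.
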